## Abstract

(1) Background: The COVID-19 pandemic has generated 771 million confirmed cases. Of these patients, 60% have developed persistent symptoms including pain. This pain is a complex symptom that needs comprehensive therapeutic strategies to address it holistically. The main objective of this study will be to evaluate the early impact of the Pain Informed Movement (PIM) program in patients with post-COVID-19 conditions experiencing new-onset persistent pain. (2) Methods: A randomized, single-blind clinical trial will be performed. Patients will be randomly assigned (1:1) to the experimental or control group. The experimental group will undergo a PIM program consisting of low-intensity functional exercises, pain neuroscience education, and relaxation techniques. The control group will receive no intervention. (3) Results: The results will be published as a peer-reviewed article. (4) Conclusions: This study will provide a basis for future research to support the implementation of comprehensive therapeutic approaches in the care of patients with post-COVID-19 persistent pain.

## 1. Introduction

The COVID-19 pandemic has represented a major medical challenge with potential long-term repercussions [1,2]. To date, more than 771 million confirmed cases have been reported [3], and approximately 60% of these patients develop persistent symptoms [4,5].

Patients are considered to have post-COVID-19 conditions when symptoms last more than 3 months [6]. Among these symptoms, post-COVID-19 persistent pain emerges as a frequent manifestation that affects the quality of life and functionality of those suffering from this condition.

Fernandez-de-las-Peñas et al. carried out an exhaustive analysis that revealed a 10% incidence of post-COVID-19 persistent pain [7]. However, previous research focused on the study of this symptom shows a frequency of 45–70% [8,9,10,11,12,13,14,15,16]. These data indicate that the magnitude of persistent pain may be underestimated in overall studies of post-COVID-19 condition patient cohorts [10,16].

The evidence available so far indicates that the experience of persistent pain in post-COVID-19 condition patients follows a nociplastic pain model [17,18]. Nociplastic pain is defined by an exacerbated sensitivity to pain and is characterized by a chronic central sensitization process that is enhanced over time [19,20] by symptoms related to the central nervous system such as psychological distress, mood disturbances, and sleep disorders [21,22,23,24].

Post-COVID-19 persistent pain presents a unique complexity, with multiple contributing factors beyond the initial respiratory implications. The patient-centered approach [25,26] based on an understanding of pain as a multifaceted phenomenon, reflects the need for holistic therapeutic interventions to address post-COVID-19 persistent pain.

To address this complexity, the need arises for comprehensive therapeutic strategies that not only address the painful symptomatology but also address potential implications at the neuromuscular and psychological levels. In this context, the Pain Informed Movement (PIM) [27] program is presented as a novel approach that combines low-intensity functional exercises, relaxation techniques, and pain neuroscience education.

The main objective of this study will be to evaluate the early impact of the PIM program in patients with post-COVID-19 conditions experiencing new-onset persistent pain. Through the implementation of this program, we seek to determine whether such intervention can offer significant improvements in reducing pain intensity and interference, catastrophizing, kinesiophobia, and functionality in patients affected with post-COVID-19 conditions.

## 2. Materials and Methods

### 2.1. Design

The study will be a randomized, single-blind clinical trial to analyze the effect of the PIM program on patients with post-COVID-19 conditions experiencing persistent pain. This group will be compared with a control group. The research assistant collecting the data will be blinded to the hypothesis of the study and the patient’s allocation. Because of the nature of the intervention, it will not be feasible to blind the participants. The protocol of this study has been registered in Clinicaltrials.gov: NCT05475743.

### 2.2. Ethical Considerations

The study protocol was approved by the Local Research Ethics Committee with registration number 2392/CEIH/2021. It will be conducted following the 1975 Declaration of Helsinki, as revised in 2013 [28], and the Consolidated Standards of Reporting Trials (CONSORT) [29]. An informed consent form will be signed by the participants after being informed about the study conditions.

### 2.3. Setting

This study will be conducted at the Faculty of Health Sciences of the University of Granada (Spain). Participants will be recruited from the Long-COVID Regional Association (Long-COVID Andalucía).

### 2.4. Participants

This study will include patients over 18 years of age with a diagnosis of post-COVID-19 with new-onset moderate or severe pain. According to the World Health Organization (WHO) definition, patients present post-COVID-19 condition when they have persistent symptoms up to 3 months after the onset of the disease, lasting at least 2 months with no alternative diagnosis that explains these symptoms [6]. In addition, moderate or severe pain not limited to a specific anatomical district or origin will be assessed with a score greater than or equal to 3.5 using a Visual Analog Scale (VAS) [30]. Patients will be excluded if they present any of the following conditions: pulmonary, cardiac, neurological, vascular, or orthopedic pathologies that may limit the performance of the assessment and the intervention, cognitive impairment that prevents them from understanding and answering the questionnaires, or if they suffer reinfection by SARS-CoV-2. In addition, those patients with a history of severe or critical illness due to COVID-19 [6] and with pre-existing chronic pain according to the current International Association for the Study of Pain definition [31,32] will be excluded. Finally, patients who participated in other studies will also be excluded.

### 2.5. Randomization

Participants in this study will be randomly assigned to two groups: the experimental group and the control group. The eligibility of participants will be assessed by an impartial professional who will not be involved in the randomization process. The randomization will be performed by an independent researcher who will not be involved in the evaluation or treatment of participants. The patients will be assigned to their respective groups sequentially. A computer program (https://www.randomizer.org) (accessed on 1 August 2023) will be used to generate a 1:1 ratio randomization sequence. The allocation sequence will be generated and maintained off-site at the study site. The information on the allocation of patients to the intervention or control group will be transmitted by mail to the recruiter. The evaluation will be carried out by a physical therapist blinded to treatment assignments.

### 2.6. Intervention

The experimental group will be included in an 8-week PIM program. This program will include pain neuroscience education, functional exercise, consisting of low-intensity strengthening exercises, and relaxation techniques. The Template for Intervention Description and Replication (TIDieR) checklist [33] will be used. The control group will receive a leaflet. Patients in both groups will be allowed to take pharmacological treatment (paracetamol or non-steroidal anti-inflammatory drugs) if needed and under the prescription of a physician. Patients’ evaluations will be conducted at baseline (T1) and immediately post-intervention (T2).

#### 2.6.1. Experimental Group

The patients included in the experimental group will attend an 8-week PIM program in addition to standard medical care. The program is based on a previous study [27] and will be led by a physical therapist with experience in treating patients with chronic pain. This program will consist of 2 face-to-face sessions per week, and they will be asked to complete two sessions at home weekly. The first face-to-face session will be a group session with 3–6 participants, and the second face-to-face session will be individual. Both sessions will last approximately 1 h. In the group sessions, pain neuroscience education will be conducted. In the individual sessions, an individualized functional exercise program will be performed by each patient, as well as relaxation techniques. Patients will be asked to perform the functional exercises and relaxation techniques at home. Participants will be asked to record their compliance with the program and their progress.

Education in pain neuroscience is considered an important pillar in the comprehensive approach to persistent pain. Multiple studies support its use in patients with this complex symptom. This technique will allow the patient to better understand the complexity of the nervous system and the pain process. In this way, education in pain neuroscience will allow the therapist to provide the patient with the cognitive tools necessary to understand and adequately manage pain.

Pain neuroscience education will consist of group sessions in which simple explanations will be given on the difference between tissue damage and pain, especially in the case of chronic pain, central nervous system level nociception processing, pain modulatory signals, neuroplasticity and adaptability of other systems, and the relationship between stress, thoughts, emotion, and pain. The fundamental objective of this technique is to explain to the patient how the human being processes and perceives pain. The use of this technique will help the patients to understand their own experiences. Improving the patients’ knowledge of pain allows them to discard all the stigmas associated with persistent pain and will give them tools that will allow them to be active in their treatment.

The first point when applying this technique in patients with persistent pain is to disprove all the inherited erroneous beliefs that the patient may have. The main erroneous belief that must be disproved is the association between pain and tissue damage. The aim is to make the patient understand that pain is a multifaceted phenomenon, influenced by physical, cognitive, and emotional factors. Once the patient understands this, he/she will be able to break the cycle of anxiety and stress associated with persistent pain.

The second fundamental point of this educational technique is the explanation of the concept of brain plasticity. The assimilation of this concept by the patient will allow him/her to understand that the nervous system is not something static but can modify itself over time.

The third and last point is to provide patients with the necessary tools to address the emotional problems that are linked to persistent pain. The connection between catastrophizing, kinesiophobia, and persistent pain is explored, thus allowing an improvement in mental health associated with better management of persistent pain. This new perspective for patients gives them hope and confidence in adopting therapeutic strategies that will enable them to manage pain in the long term. In this way, persistent pain is no longer an experience full of unknowns and doubts, but a challenge that can be addressed.

The functional exercise program will consist of 3 different parts. The first part will be a warm-up focused on joint mobilization. The second part will focus on functional exercises consisting of low-intensity strengthening exercises of the main muscle groups. This section will have four main objectives: core stability, postural positioning, limb muscle strength, and functional activities. The proposed exercises have been previously used in this population demonstrating their reliability and safety [34,35]. Some of them are the bodyweight squat, hip thrust, rowing, front plank, lateral squat, and chest press. However, the exercises, the number of sets and repetitions, and rest periods will be individually adapted to each patient depending on their needs, severity of pain, and physical ability with different levels of progression. The exercises will be adapted so that they can be performed at home without the need for specific materials. Only when the patient can perform the exercises with the correct technique and without effort, the exercises will be progressed to more demanding exercises or a higher training load.

Finally, relaxation techniques will be performed. Relaxation strategies will include practicing mindfulness and breathing control, cultivating body awareness and muscle tension management, as well as awareness of thoughts and emotions related to pain.

The mindfulness practice will focus on trying to make the patient aware of the present moment. To do this, the patient will be asked to focus their attention on the bodily sensations they have at that moment and on their breathing rhythm. The goal is to allow the patient to disconnect from the persistent pain, focusing on healthy sensory experiences. Breathing control is a fundamental technique to improve the stress response. Participants should practice deep and conscious breathing, which will allow a more efficient oxygen intake and carbon dioxide output, thus contributing to reducing the activation of the sympathetic nervous system and therefore the perception of pain.

The body awareness and muscle tension management techniques will be performed through exercises that allow patients to develop a greater awareness of areas of tension. Increased body awareness will allow patients to become proactively involved in pain management.

Finally, cognitive change techniques will be used to improve pain-related emotions. Patients will be asked to identify negative thought patterns and redirect them towards more positive and constructive thoughts. The aim of performing these techniques is to contribute to a better management of the psychological impact of persistent pain.

The set of relaxation techniques is one of the essential components of this intervention program. It is intended that these techniques not only help to alleviate the painful symptomatology but also to promote proactive changes, improving the patient’s self-regulation and quality of life, thus helping to generate a better overall experience.

During the face-to-face sessions, participants will be asked to perform the functional exercises and relaxation techniques at home. They will also be asked to record this so that the therapist can follow up properly. Participants will be free to ask any questions during the program.

#### 2.6.2. Control Group

In addition to standard medical care, patients assigned to this group will receive a leaflet with information about the main post-COVID-19 condition symptoms. This is a control group that will not be controlled or monitored by a therapist.

### 2.7. Outcomes

Patients will be initially contacted by telephone. Patients will be informed of the study and if they agree to participate a face-to-face appointment will be arranged. The initial evaluation will be performed once informed consent is obtained. The sociodemographic characteristics collected will include the anthropometric data, weeks since infection, percentage of smokers, comorbidities assessed with the Charlson comorbidities index [36,37], physical activity through the International Physical Activity Questionnaire Short Form (IPAQ-SF) [38] and working activities by self-report. In addition, patients will be asked to complete a diary with the pharmacological pain treatment they are taking.

#### 2.7.1. Primary Outcomes

Pain intensity and interference will be quantified using the Brief Pain Inventory (BPI). The section intended to measure pain intensity on the BPI comprises four items, while the section related to pain interference includes seven items. In the intensity section, responses range on a scale from 0 (no pain) to 10 (maximum pain), while in the interference section, responses range from 0 (no interference) to 10 (total interference). To calculate the severity and interference index, the values of the corresponding items are averaged, obtaining values ranging from 0 to 10, with a higher score indicating greater pain intensity and interference. In addition, body spatial pain distribution will be marked on a predetermined diagram provided in this inventory. The BPI has been validated as a reliable and valid tool to evaluate these aspects of pain [39,40]. The Spanish version of this scale has demonstrated high internal consistency, with an alpha coefficient of 0.93 [41].

To evaluate the phenomenon of catastrophizing, the Pain Catastrophizing Scale (PCS) will be applied [42]. This instrument consists of 13 statements structured on a 5-point Likert scale ranging from 0 (at no time) to 4 (at all times). The PCS breaks down catastrophizing into three components: feelings of helplessness, magnification of difficulties, and rumination about pain [43,44]. Each of the items describes different thoughts and emotions that people may experience when in pain. The final score is obtained by summing the scores of all the items, resulting in a score ranging from 0 to 52, with higher scores indicating a higher level of catastrophizing. It is important to note that the Spanish version of this scale, used in this study, has demonstrated adequate internal consistency, with an alpha coefficient of 0.79 [45].

The Spanish translation of the Tampa Kinesiophobia Scale (TSK) will be used to quantify apprehension related to physical activity and the fear of injury (or re-injury). This scale is composed of 11 statements, which are assigned a score on a 4-point scale (1–4). Total scores vary between 11 and 44 points, with higher values being indicative of greater fear of movement and the possibility of (re)injury. In the Spanish version of this scale, a moderate internal consistency has been found, with a coefficient alpha of 0.79 [46].

Functionality will be assessed using the WHODAS 2.0 tool (World Health Organization Disability Assessment Schedule) [47], using the Spanish version [48,49]. It consists of 36 items assessing six main areas of functional ability. This questionnaire uses a 5-point Likert scale for respondents to rate their level of difficulty in six main subscales: Cognition, Mobility, Self-Care, Interpersonal Relationships, Home Life, and Community Involvement. Response options go from 1 (no difficulty) to 5 (extreme difficulty or can not do). The scores obtained in each area are added to obtain a total score that shows the degree of functional limitation.

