### 2.8. Sample Size Calculation

An a priori sample size was based on the minimum clinically important difference (MCID) of the BPI interference estimated to be 1.00 [50]. Using G*Power 3.1.9.2, we obtained a sample size of 49 participants, equally distributed between the treatment and control groups, based on a confidence level of 95% (α = 0.05) and a power of 80% (β = 0.2). Anticipating a 20% dropout rate, the total sample size was increased to ensure adequate statistical power and the resulting sample size was 30 participants per group.

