### 2.9. Statistical Analysis

Data will be analyzed using the Statistical Package of Social Science (SPSS) program for Windows (version 26 IBM, Armonk, NY, USA). Categorical data will be expressed as frequency (percentage). Continuous variables will be presented as mean and standard deviation (SD). The normality of the data will be first tested with the Shapiro-Wilk test. Characteristics of both groups will be compared using the Chi-square test for categorical variables. For continuous variables, the Student *t*-test will be used for those with a normal distribution and the Mann-Whitney U test for nonparametric variables. All effect sizes will be interpreted according to Cohen’s conventions: 0.3 = small, 0.5 = moderate, and 0.8 = large. A per-protocol analysis will be performed including participants who completed the treatment plan. Statistical significance will be set at *p* < 0.05.

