With respect to functionality outcomes, many interventions have been developed to date to try to improve this variable in patients with this condition. These interventions are respiratory rehabilitation programs focused mainly on respiratory, functional, and quality of life variables. Some of these interventions have been shown to be beneficial in improving patient functionality [63,64,65,66]. In contrast, other studies have not found these differences in favor of the intervention group [67,68,69].

In addition to respiratory rehabilitation interventions, symptom control interventions have been developed in patients with post-COVID-19 conditions. In this type of intervention, the results regarding functionality are not consistent. In the study by Philip et al. [57] no significant improvements were found in the intervention group with respect to the control group. In contrast, in the study by Kuut et al. [70] significant differences were found with respect to the control group, but with a small effect size (Cohen’s d = 0.34). Further studies are needed to determine whether these types of interventions can help improve the functionality of patients with this condition.

The PIM program has been previously used in patients with osteoarthritis showing to be effective in reducing pain levels and functionality [27]. The results of our study are expected to achieve minimal detectable change for the Brief Pain Inventory and WHODAS 2.0 tools with complex scoring. If the expected results are achieved the PIM intervention program will prove to be effective in the management of persistent pain in patients with post-COVID-19 conditions.

Despite the positive results, this study has some limitations. Although the intervention proposed in this article fits the complexity of persistent pain post-COVID-19, the fact that it is a comprehensive intervention will make it difficult to determine the exact mechanisms behind patients’ improvement. Our intervention will include low-intensity functional exercise, relaxation exercises, and education in pain neuroscience, so we should consider the possible contribution of each component of the intervention. It would be interesting to design future research to investigate the efficacy of the different components of the overall intervention. Furthermore, the lack of participant blinding due to the nature of the intervention could introduce bias.

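### Five unranked primary outcomes share one p < 0.05 threshold while the trial is sized on BPI interference alone, so what counts as success is not fixed

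*Protocol article*

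**What the plan says.** The heading of section 2.7.1 of the protocol article is Primary Outcomes. Four instruments giving five outcomes stand under it:

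- BPI intensity and BPI interference, two separate 0–10 indices: "Pain intensity and interference will be quantified using the Brief Pain Inventory (BPI".
- PCS total, 0–52: "To evaluate the phenomenon of catastrophizing, the Pain Catastrophizing Scale (PCS) will be applied".
- TSK total, 11–44: "The Spanish translation of the Tampa Kinesiophobia Scale (TSK) will be used to quantify apprehension".
- WHODAS 2.0 total: "Functionality will be assessed using the WHODAS 2.0 tool".

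The next heading is 2.7.2, Covariables, so there is no secondary tier. Section 3 (Results) again refers to primary outcomes in the plural. The objective at the end of the Introduction and the opening of the Discussion list the same five constructs without ranking them.

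Section 2.8 bases the sample size on one of the five: "An a priori sample size was based on the minimum clinically important difference (MCID) of the BPI interference estimated to be 1.00". It uses α = 0.05 and 80% power.

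Section 2.9 gives one threshold for the whole analysis: "Statistical significance will be set at" p < 0.05. It states no order of testing and no rule on how many primary outcomes must succeed.

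The Discussion then says: "If the expected results are achieved the PIM intervention program will prove to be effective in the management of persistent pain". It does not say which outcome decides.

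**The concern.** A primary outcome is the one on which the trial is judged. Here five carry that label, but the sample size, and the only effect judged worth detecting, belong to one. The article does not say how the five combine into a conclusion.

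Two readings are open, and the stated design figures fit neither:

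- **Any one suffices.** The chance of at least one false positive among five tests exceeds the 5% attached to each.
- **All five are needed.** The error is controlled, but the stated 80% power refers to one outcome and not to joint success.

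At stake is what a report of success would mean. The Discussion and Conclusions speak of demonstrating effectiveness and efficacy, which is confirmatory language. Participants cannot be blinded, all five outcomes are questionnaires that they complete about themselves, and the control group receives a leaflet in addition to standard care. Freedom to choose the deciding outcome after the results are known would add an avoidable risk to a comparison whose lack of blinding the article already names as a limitation.

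**Working it through.** **Inputs from the article.** Five primary outcomes (2.7.1). One post-treatment assessment, T2, so one post-treatment between-group comparison per outcome (2.6). Threshold 0.05 (2.9). MCID 1.00 on BPI interference, α = 0.05, power 80%, 49 participants before dropout and 30 per group after it (2.8).

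**Not given, so assumed.** The correlations among the five outcomes, taken as one common value r. The SD of BPI interference and the sidedness of the sample-size test.

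**Step 1: the plan's own figure.** The 49 cannot be reproduced without an SD. Solving backwards with 49/2 = 24.5 per arm, a two-sample t-test and 80% power gives:

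- two-sided: d ≈ 0.82, so SD ≈ 1.00/0.82 ≈ 1.22;
- one-sided: d ≈ 0.72, so SD ≈ 1.00/0.72 ≈ 1.39.

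These implied effects are needed only in step 5.

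**Step 2: any-one reading, independent tests.**

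- Error in either direction: 1 − 0.95^5 = 1 − 0.774 = 22.6%.
- Error in favour of the programme only: 1 − 0.975^5 = 1 − 0.881 = 11.9%, against a nominal 2.5%.

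**Step 3: any-one reading, correlated tests.** Five normal test statistics with common correlation r were simulated under no effect (500,000 draws per value), each compared with ±1.96.

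| Assumed r | At least one false positive, either direction | At least one in favour of the programme |
|---|---|---|
| 0 | 22.6% | 11.9% |
| 0.3 | 20.9% | 10.4% |
| 0.5 | 18.3% | 9.2% |
| 0.7 | 14.9% | 7.4% |
| 0.8 | 12.8% | 6.4% |
| 0.9 | 10.2% | 5.1% |

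The first column compares with a nominal 5%, the second with 2.5%. Even at r = 0.9 both are about twice nominal.

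**Step 4: all-five reading.** The error of a joint claim cannot exceed the 0.05 of any single test, so there is no inflation. Joint power, however, cannot exceed the power of the weakest of the five tests, so it is at most the 80% claimed for BPI interference. As an illustration, if each outcome had 80% power and the tests were independent, joint power would be 0.8^5 = 0.328, or 33%; positive correlation moves this up towards 80%. The article gives no effect or SD for the other four outcomes, so the actual value cannot be placed within that range, and it could be lower still if any of them is less well powered.

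**Step 5: what keeping five primaries would cost.** Bonferroni gives 0.05/5 = 0.01 per test.

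- With the two-sided back-solved d ≈ 0.82, power for BPI interference falls from 80% to about 57% at 24.5 per arm (56% at 24). Restoring 80% takes 37 evaluable per arm; 37/0.8 = 46.25, so 47 per arm, or 94 in total against the planned 60.
- If the sizing was one-sided (d ≈ 0.72), power at 0.01 with 24 per arm is about 43%.

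Both rest on an effect size that the article does not state.

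**The case against.** **The any-one rule is not in the text.** The expectations are worded jointly: the Discussion adds catastrophizing, kinesiophobia and functionality to pain, and the Conclusions speak of pain relief together with better functionality. This stands. The inflated error is conditional on a rule that the article neither states nor excludes, so no single error rate can be attributed to the plan. It does not rescue the design, because the joint reading leaves the sample size describing only one of the five requirements.

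**The two-sided figures overstate the risk of a false claim of benefit.** This stands too. A wrong claim of effectiveness needs an error in favour of the programme, for which the figures are 7% to 12% at r from 0.7 to 0. Independence is also the least plausible case, since two outcomes come from the same inventory and all are self-reported.

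**Multiplicity methods are commonly left to an analysis plan.** Agreed, and the absence of a named method is not the point. A reader might infer from section 2.9 that every test is unadjusted, but the text does not say so; adjusted p-values can also be compared with 0.05. What the article does fix is five primaries alongside a sample size that spends the full 0.05 on one of them. A later division of alpha would conflict with section 2.8.

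**Other inferences to resist.** The Discussion's mention of minimal detectable change on the BPI and WHODAS might be read as a second, competing success criterion. It is an expectation, not a decision rule, and it does not contradict sizing on an MCID. Nor is there support for a higher error through testing of PCS components or WHODAS domains: section 2.7.1 defines a total score for each, and no subscale test is planned.

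**The aims are modest.** The article speaks of early impact and a basis for future research. It also says that it aims to demonstrate efficacy, so the primary outcome still has to be settled.

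**Conclusion.** The concern holds in this form: five unranked primary outcomes, one threshold, a sample size for one of them, and no statement of what constitutes success.

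Under an any-one rule, the two-sided family-wise error is about 15% to 23% for an assumed common correlation of 0.7 down to 0, and about 10% at 0.9. In favour of the programme only, it is about 7% to 12% for r from 0.7 to 0, and about 5% at 0.9, against 2.5%. Under an all-five rule the error is not inflated, but the stated 80% is at best an upper limit on the power for success. The correlations are assumptions, and the choice between the two readings is open.

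A flat statement that the trial runs a 22.6% risk of a false claim of effectiveness would go too far. That figure needs the any-one rule and independent outcomes, and it also counts errors favouring the control group.

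**What to change.** - In section 2.7.1, name the between-group difference in BPI interference at T2 as the single primary outcome. The sample size already uses BPI interference.
- Make BPI intensity, PCS, TSK and WHODAS 2.0 secondary. Either test them in a fixed order or with Holm adjustment, or report them with 95% CIs and no confirmatory claim.
- In section 2.9, attach the 0.05 threshold to the primary comparison and state how the secondary outcomes are handled.
- In the Discussion, base the conclusion on effectiveness on BPI interference, with its 95% CI read against the 1.00 MCID.

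The sample size, alpha and study procedures do not change. This is cheaper than keeping five primaries with divided alpha, which would need more participants or accept lower power.

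The cost is that four outcomes lose stand-alone confirmatory status. The change also needs a dated protocol amendment before unblinded analysis. The trial is registered, and the registry record was not available here; if it lists the same primary outcomes, it should be updated at the same time, openly and with the reason given.
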